### Follow Up Strategy

This population can be difficult to follow-up and loss to follow-up in this setting has been reported as high as 48% [38]. Therefore, the research nurse will take an address and telephone details for the patient or relative/carer. The patient will also be asked to give permission for the research team to contact their General Practitioner (GP) to obtain additional data. To facilitate ease of access for treatment and follow-up, patients will be offered a range of follow-up options either in the hospital, on the telephone, or at home. Two weeks prior to the follow-up appointment, the patient or other named contact will be contacted to determine if they will be attending their appointment. The day before their appointment, patients will be contacted to remind them that their follow-up appointment is due the next day. If the patient is unable to be contacted, they will be sent a letter asking them to contact the team in order to arrange follow-up. If the patient is unable to be contacted via telephone or fails to respond to a letter for the 6 month follow-up appointment, the research nurse will visit the patients home to determine a) if the patient still resides at that address, and b) if the patient is still willing to undertake a follow-up appointment. If the patient cannot be contacted by the team at this stage, they will be said to be lost to follow-up.

### Ethical Considerations

Each group will receive normal clinical care in their respective groups. No patient group will be disadvantaged as clinical care in these patients varies, and we do not know which the most effective treatment is.

### Planned Analysis

An intention to treat analysis (ITT) will be performed on all analyses. This will include all patients assigned to the two groups; EBI or standard care as randomised, irrespective of the patient's compliance with the study protocol or the actual study intervention received. A per protocol analysis will also be performed. The per protocol analysis will comprise all patients in the ITT population who have met all the following major inclusion criteria and who do not have any major protocol violation. A sensitivity analysis will be applied for any missing primary outcome data.

To ensure the appropriateness of the event rates used in this sample size calculation, an internal pilot is planned after 160 patients will have been randomised. The two main reasons for performing the internal pilot are:

• Evaluation of overall proportion of patients displaying a fall in SADQ score to compare the estimate used in the original sample size calculation.

• Monitoring study recruitment and missing data for all primary and secondary outcomes.

The only outcome data that will be analysed within the internal pilot analyses is the proportion of patients displaying a fall in the primary outcome of the study (SADQ) between baseline and 12 weeks' follow-up. The results will be presented as numbers and percentages and the proportion of patients showing a fall in SADQ used in the original sample size calculation will also be checked by using the estimates that are obtained from the internal pilot analysis. Outcomes showing unexpected missing information will be highlighted and discussed with members of the Independent Trial Steering Committee (ITSC). If sample size recalculation suggests need for more patients to preserve power to detect treatment effect, then on the advice of the ITSC, we will aim to increase recruitment and consider implications for funding and existing resources.

### Analysis of primary outcomes

The primary endpoint is a fall in SADQ at 6 months post randomisation. Test scores will be summarised using descriptive statistics, means with 95% confidence intervals (or medians with inter-quartile ranges if non-normally distributed) at baseline, and 6 months. The hypothesis of no difference between the two treatment arms at 6 months (separate analyses) will be tested using analysis of covariance (ANCOVA), controlling for baseline measurements. A p-value of 0.05 (5% level) will be used to declare statistical significance and 95% confidence intervals of the estimated effects will be reported. Time by treatment interaction will be assessed. The primary analysis using ANCOVA will not adjust for any missing data. However, reasons for missing outcome data will be reported and a sensitivity analysis will be undertaken. The assumptions that are made when using ANCOVA (i.e. normality of scores at treatment levels, homogeneity of variance, homogeneity of regression slopes, linear regression) will be assessed. If unequal variances, nonlinearity and/or non-parallel slopes are present, a suitable transformation of scores will be employed to improve the linearity and to promote equality of the variances.

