### Primary outcome measures

As in previous research by our team, the primary outcome measure for the study is the change in SADQ score at 6 months post randomisation. The SADQ is a short 20-item questionnaire designed to measure severity of dependence on alcohol [40]. There are five subscales with four items in each: Physical Withdrawal, Affective Withdrawal, Withdrawal Relief Drinking, Alcohol Consumption, and Rapidity of Reinstatement. Each item is scored on a 4-point scale, ranging from "Almost Never" to "Nearly Always" resulting in a corresponding score of 0 to 3. Thus the total maximum score possible is 60 and the minimum is 0.

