### Sample Size calculation

Based on a previous study by ourselves on dependent drinkers receiving interventions from an ASN, it is expected that 55% of such patients will display a fall in SADQ score between baseline and 12 weeks' follow up [38]. Another confounder in this area of research is the phenomenon of natural recovery (NR). The NR rate over this time period expected in the control group is expected to be no more than 25% (the literature ranges from 12% with a treatment population [40] up to 35% within a general lifetime population [43,44]). In order to detect this difference between the groups (55% vs. 25%) with 90% power at the 5% significance level, approximately 65 patients are required in each group. In order to allow for an estimated 50% drop out rate (observed in previous studies in similar patients), 130 patients will be recruited per group. It is estimated that at least 5 eligible patients will be recruited per week, and thus this target should be achieved within the 12 month recruitment period.

A fall in SADQ at 6 months is be the primary outcome. As there were few studies that report SADQ scores at baseline and follow-up, the revised power calculation was based on the our own studies that 22% vs 53% fall in SADQ between control and Intervention arms at 6 months. In order to detect this difference between the groups (55% vs. 25%) with 90% power at the 5% significance level, the required size is 103 (51 per group), and 206 (103 per group) once adjusted for 50% dropout.

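### The 90% power is calculated for the proportion of patients with a fall in SADQ, but the primary test is ANCOVA on the SADQ score, whose power is not stated

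*Protocol article*

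**What the plan says.** **Endpoint.** Under Primary outcome measures, "the primary outcome measure for the study is the change in SADQ score at 6 months post randomisation", on a scale from 0 to 60. The Abstract likewise names the level of dependence given by the SADQ score. Under Analysis of primary outcomes the wording shifts: "The primary endpoint is a fall in SADQ at 6 months post randomisation".

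**Test.** The same section says that the hypothesis of no difference between arms at 6 months "will be tested using analysis of covariance (ANCOVA), controlling for baseline measurements". The assumptions to be checked are "normality of scores at treatment levels, homogeneity of variance, homogeneity of regression slopes, linear regression", with transformation of the scores if they fail. These are checks for a continuous outcome.

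**Sample size.** The first calculation rests on a yes/no event: "it is expected that 55% of such patients will display a fall in SADQ score between baseline and 12 weeks' follow up". The control rate is "expected in the control group is expected to be no more than 25"%. This gives about 65 evaluable patients per group, or 130 after 50% dropout. The revised 6-month calculation uses 53% against 22% from the sponsor's own studies. It then repeats 55% against 25%, and arrives at 51 per group, or 103 after dropout. Both claim 90% power at the 5% level.

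**Internal pilot.** Planned Analysis calls these figures event rates. After 160 randomisations, the only outcome examined is the proportion of patients with a fall in SADQ. Recruitment may be increased on that basis.

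**The concern.** A sample size supports a trial only for the comparison it was calculated for. Here the calculation is for two proportions and the primary test compares adjusted mean scores. The two use different information: the first ignores how far each patient's score moves, and the second depends on it. Without a mean difference, an SD and a correlation with baseline, the power of the planned test cannot be recovered from the document.

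Two things follow. A null ANCOVA result could not be read against the stated 90%. And the internal pilot could raise the sample size, or leave it alone, on a quantity that does not determine the power of the primary test.

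**Working it through.** **Inputs from the protocol.** Rates of 53% and 22% (revised) and 55% and 25% (first calculation); 51 or 65 evaluable per group; 90% power; 5% level. Sidedness is not stated, so two-sided is assumed.

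**Step 1. Reproduce the stated size.** With p̄ the mean of the two rates,

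n = [1.96·√(2p̄(1−p̄)) + 1.2816·√(p₁(1−p₁)+p₂(1−p₂))]² / (p₁−p₂)²

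- 53% against 22%: (1.342 + 0.831)² / 0.0961 = 49.1, so 50 per group (stated: 51).
- 55% against 25%: (1.358 + 0.845)² / 0.09 = 53.9, so 54 per group. The unpooled variance gives 50.8, so 51.
- Power at 51 per group is 91% for 53%/22% and 88% for 55%/25%.

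On either pair of rates, 51 is a two-proportion size. (The first calculation's 65 is larger than the 54, or 61 with continuity correction, that its rates need. That is a separate matter.)

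**Step 2. What the ANCOVA detects with 90% power.** With ρ the correlation of baseline and 6-month SADQ, which is not given and is assumed here,

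δ/SD = (1.96 + 1.2816)·√(2/n)·√(1−ρ²)

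| Evaluable per group | ρ = 0 | ρ = 0.5 | ρ = 0.7 |
|---|---|---|---|
| 51 | 0.64 | 0.56 | 0.46 |
| 65 | 0.57 | 0.49 | 0.41 |

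**Step 3. Do the protocol's rates fix the ANCOVA power?** Two assumed models of change, both with 53% and 22% falling and 51 per group:

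- *Normal change scores, equal SD.* The implied difference is z(0.53) − z(0.22) = 0.075 + 0.772 = 0.85 SD of change. Power = Φ(0.847·√(51/2) − 1.96) = Φ(2.32), about 99%. For 55%/25% the difference is 0.80 SD and power about 98%. Baseline adjustment would not be expected to lower this.
- *Arms differ only in the share who fall; sizes of falls and rises exponential.* With both means at 5 points, mean change is −0.30 (EBI) and +2.80 (control), a difference of 3.10. The SDs are √(50 − 0.09) = 7.06 and √(50 − 7.84) = 6.49, which combine to 6.78. The difference is then 0.46 SD, and power = Φ(0.457·√(51/2) − 1.96) = Φ(0.35), about 64%. Simulated ANCOVA with mean falls of 5 to 20 points and mean rises of 0.5 to 5 points (assumed baseline mean 30, SD 12) gave roughly 57% to 71%, depending on those means and on whether scores were held within 0 to 60. With the same data, the test of proportions keeps about 91%.

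The same pair of rates is thus compatible with ANCOVA power from about 60% to about 99%.

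**The case against.** The strongest reply is that only one primary test is written down. The Abstract, Primary outcome measures and the ANCOVA text all concern the score. A fall in SADQ can be read as the hoped-for direction of change, and no section compares the proportion between arms. This stands. A reader might infer two rival primary analyses from which to choose after the data are seen; the document does not support that. What it has is one test, loose endpoint wording and a power figure from elsewhere.

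A reader might also infer that the trial is underpowered. Step 3 does not show this, because under normal change scores the ANCOVA exceeds 90%. Nor is a significant ANCOVA irrelevant to the hypothesis: a mean difference bears on it without testing the proportions.

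It is tempting to add that the control rate is too low, since natural recovery is cited up to 35%. But that rate supports only the first calculation, the 35% is described as a general lifetime figure, and the revised 22% is attributed to the sponsor's own studies. An argument that measurement noise alone would produce many small falls needs an SD and a retest reliability that the protocol does not give.

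Finally, the revised percentages might be read as mean percentage falls. The arithmetic in Step 1 and the event-rate wording under Planned Analysis point to proportions. Even on the other reading, no SD is given.

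**Conclusion.** The point holds as a mismatch between the sample size calculation and the primary test. The stated 90% power is reproduced, to within rounding or choice of variance formula, by a comparison of proportions that the protocol does not plan. The planned ANCOVA has no stated power.

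The size of the error cannot be given as one number. At 53% against 22% and 51 per group, power lies between about 60% and 99% under the assumed distributions, so it may fall well short of 90% or exceed it. The detectable differences in Step 2 rest on a two-sided 5% level, the normal approximation and assumed correlations.

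The validity of the ANCOVA and its 5% level are not in question. The defect lies in the justification of the sample size, the wording of the endpoint, and the parameter the internal pilot monitors.

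**What to change.** 1. **Analysis of primary outcomes:** name one primary endpoint, SADQ score at 6 months, compared by ANCOVA adjusted for baseline SADQ and reported as an adjusted mean difference with 95% CI. Remove the fall in SADQ as an alternative definition.
2. **Sample Size calculation:** replace the 90% power statement with the difference that the evaluable number detects by ANCOVA (Step 2, for 51 or 65 per group, whichever target is kept). Convert it to SADQ points with the SD from the sponsor's earlier studies, and say why a difference of that size is worth detecting.
3. **Planned Analysis:** have the internal pilot check the pooled SD of SADQ and its correlation with baseline instead of the proportion with a fall. Both can be estimated without comparing the arms.
4. Report the proportion with a fall as a supportive result only.

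The cost is text changes in three sections, with no added data collection. The stated power becomes a detectable difference, and the sponsor must retrieve an SD, and preferably a correlation, from its earlier data. If that difference in SADQ points proves too large to be plausible, the sample size would have to be reconsidered.

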### Missing data and missing questionnaire items

To investigate how sensitive the results of the primary and secondary analysis are to missing data a number of strategies will be used including joint modelling as well as imputing values for missing longitudinal scores at 12 weeks and 6 months. The results of the sensitivity analyses will be compared to assess the relative effect of missing data on the conclusions of the primary and secondary analysis.

For a scale which is based upon a number of items, of which one or more is missing, to investigate how sensitive the results of the primary analysis are to missing data a number of strategies will be used including a simple imputation where we will estimate the scale score for the missing items from the mean of those items which are available and this mean is then used to replace the two missing values. Missing scale scores will also be imputed with worst-case value, with best-case value and model-based imputation.

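### With 50% dropout expected, the primary 6-month ANCOVA leaves out about half of the patients promised in the ITT analysis and uses the 12-week SADQ only in sensitivity analyses

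*Protocol article*

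**What the plan says.** Under Planned Analysis the protocol applies intention to treat to every analysis and defines the set by allocation: "This will include all patients assigned to the two groups; EBI or standard care as randomised". Under Analysis of primary outcomes the 6-month comparison is an ANCOVA controlling for baseline, and "The primary analysis using ANCOVA will not adjust for any missing data". Reasons for missing data are to be reported, and a sensitivity analysis follows.

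The expected loss is large. Sample Size calculation says "In order to allow for an estimated 50% drop out rate (observed in previous studies in similar patients), 130 patients will be recruited per group", and the revised calculation in the same section again adjusts for 50% dropout. Follow Up Strategy adds that "loss to follow-up in this setting has been reported as high as 48" per cent.

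SADQ is measured at 12 weeks: the internal pilot under Planned Analysis uses the fall from baseline to 12 weeks. Missing data and missing questionnaire items lists joint modelling, "imputing values for missing longitudinal scores at 12 weeks and 6 months", and worst-case, best-case and model-based imputation. All of these are sensitivity analyses, and none is named as the leading one.

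**The concern.** A patient without a 6-month SADQ cannot enter a single-visit ANCOVA that makes no provision for missing outcomes. The main test is therefore a complete-case analysis of about half the trial, although the protocol says the analysis covers everyone assigned.

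Such an analysis is unbiased only if, given arm and baseline SADQ, loss is unrelated to the 6-month outcome. That is a demanding condition here. How a patient is drinking at 12 weeks may well affect whether that patient is seen at 6 months. EBI patients are offered up to six sessions in the first 12 weeks and controls none, so the link between drinking and loss could differ by arm. Bias in either direction is then possible in the result that carries the primary p-value. The 12-week SADQ, the measurement most likely to help, is not in that model.

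**Working it through.** **1. The plan's own numbers.** The revised calculation gives two pairs of rates, "22% vs 53% fall in SADQ between control and Intervention arms at 6 months" and then 55% against 25%. That is a separate matter and does not affect this point. Two-sided 5% is assumed, with 90% power and 1:1 allocation.
- 53% against 22%, pooled variance: n = [1.960·√(2·0.375·0.625) + 1.282·√(0.2491 + 0.1716)]² / 0.31² = 49.1, so 50 per group.
- 55% against 25%, unpooled variance: n = (1.960 + 1.282)²·(0.2475 + 0.1875) / 0.30² = 50.8, so 51 per group.
- Stated: 103 evaluable (51 per group). This is reproduced to within two patients per group.
- Dropout: 103 / (1 − 0.5) = 206. In the first calculation, 65 / (1 − 0.5) = 130 per group.

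The trial is sized on completers: 103 of 206 patients, or 130 of 260, are expected in the primary test.

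**2. What half the data leaves open.** This step uses the responder rates of the sample-size section as an illustration, since the ANCOVA itself works on scores. Take 51 of 103 observed per arm, so f = 51/103 = 0.495, with 53% against 22% among completers.
- Every missing EBI patient improves and no missing control does: 0.31·0.495 + 0.505 = +0.66.
- The reverse: 0.31·0.495 − 0.505 = −0.35.
- No missing patient improves: 0.31·0.495 = +0.15.

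A completer difference of 31 points is thus compatible with −35 to +66 points among all randomised. These are extreme bounds, not forecasts.

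**3. Bias under assumed loss mechanisms.** The documents give no SD, correlations or 12-week follow-up rate. Assumed: SD 12; correlations 0.5 (baseline and 12 weeks), 0.4 (baseline and 6 months) and 0.7 (12 weeks and 6 months); 65% seen at 12 weeks and 50% at 6 months; 103 per arm; no true effect; 3000 simulated trials per scenario. Complete-case ANCOVA is compared with a likelihood estimator that also uses the 12-week score.

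| Loss mechanism | Complete-case bias (SADQ points) | Complete-case false positives | Bias using 12-week score |
|---|---|---|---|
| Poor 12-week score raises loss, EBI arm only | −1.3 | about 10% | 0.0 |
| Opposite directions in the two arms | −2.8 | about 25% | under 0.1 |
| Same dependence in both arms | within 0.05 of zero | 4% to 5% | – |
| Random | none | – | none |

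With random loss the SD of the estimate is 2.17 (complete case) against 2.08, and 1 − 2.08/2.17 = 4%.

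**4. A second set of assumptions.** Here the 12-week score is available for everyone, correlations are 0.5 between baseline and each follow-up and 0.7 between follow-ups, the log-odds of loss rise by 1 per SD of 12-week score, and there are 2000 runs.
- EBI-only dependence, no true effect: complete-case bias −0.19 SD (0.19·12 = 2.3 points at SD 12) and 19% rejection. The estimator using the 12-week score has bias 0.00.
- Same dependence in both arms: bias 0.01 SD with no true effect. A true −0.50 SD is estimated as −0.46.

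**5. Where the remedy stops.** If patients seen at 6 months were also seen at 12 weeks, 65% − 50% = 15% of those randomised supply a 12-week score but no 6-month score. That is about 0.15·206 = 31 patients; the other 35% have no follow-up score. With loss differing in the EBI arm only:
- If 12-week attendance itself depends on drinking, the bias is about −1.8 to −2.1 points and is practically the same with either method.
- If loss depends on 6-month drinking, the bias is −2.4 (complete case) against −1.5 (likelihood model).

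**The case against.** The protocol does not ignore missing data. It names joint modelling, longitudinal imputation and extreme-case imputation, will report reasons for loss, and sets out active tracing up to a home visit before a patient counts as lost at 6 months. The detail of those methods belongs in an analysis plan that is not shown. ITT is defined by allocation regardless of compliance, the same paragraph provides for missing primary outcomes, and the complete-case choice is stated openly. All of this stands. It narrows the point but does not remove it, because the primary test itself is fixed as complete-case and half the sample is expected to be missing from it.

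A reader might infer several stronger things that the documents do not support:
- **That the analysed half is known to be a biased selection.** Nothing in the protocol says loss differs by arm or follows drinking. With the same mechanism in both arms, bias is close to zero under the null.
- **That the 12-week SADQ is thrown away.** It is absent from the primary model only; the sensitivity analyses can use it.
- **That the promised time-by-treatment interaction cannot be obtained.** The protocol says it will be assessed, not that it will come from the single-visit ANCOVA, and joint modelling could supply it.
- **That best-case and worst-case imputation is wrong.** It gives legitimate bounds; preferring a delta-adjusted analysis is a choice among accepted methods.
- **That a repeated-measures model would remove the bias.** It does so only when loss depends on scores that were observed (step 5).

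**Conclusion.** The point holds as a conflict within the protocol and a weak choice of primary analysis. ITT on all assigned patients, 50% dropout and a 6-month ANCOVA with no provision for missing outcomes do not fit together: about half of those randomised would not contribute to the primary test.

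How much harm this does depends on why patients are lost. Under assumed inputs the false-positive rate is about 10% to 25%, with bias of −1.3 to −2.8 SADQ points, when loss follows 12-week drinking differently by arm. There is little bias under the null when it works alike in both arms, and a true effect may then be somewhat understated. With random loss the only cost is about 4% in standard error. The arm-specific mechanism is plausible because of the extra EBI contacts, but it remains an assumption, as do the SD, the correlations and the 12-week follow-up rate. The expected loss, the analysis set and the model are the protocol's own.

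**What to change.** Settle the following before outcomes are seen by arm:
- Make the primary analysis a repeated-measures likelihood model of the 12-week and 6-month SADQ with baseline SADQ, arm, visit and arm-by-visit terms, and the 6-month arm contrast as the primary result. Alternatively, use multiple imputation by arm that includes the 12-week scores and record-based service use, which does not depend on attending an interview.
- Keep the complete-case ANCOVA as a sensitivity analysis.
- Name one missing-not-at-random analysis as the lead sensitivity analysis, so that it is not chosen after the results are known.
- Reword the ITT statement to say which patients are actually analysed and how those without a 6-month score are handled.

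The cost is wording and modest programming; no new data are needed. The new primary analysis assumes missing at random. The repeated-measures model gains follow-up information only from patients seen at 12 weeks, so it will not remove bias from patients lost before then. That is why the lead missing-not-at-random analysis is needed as well.
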